# Telemedicine-based antibiotic stewardship program in pediatrics: study protocol of a stepped wedge cluster randomized trial—the TeleKasper study

**DOI:** 10.1186/s13063-024-08493-z

**Published:** 2024-10-14

**Keywords:** Antimicrobial stewardship, Telemedicine, Randomized controlled trial, Pediatrics

## Abstract

**Background:**

Overuse and misuse of antibiotics is one of the driving factors of antimicrobial resistance, a growing global health threat. The use of antibiotics is particularly high in children. Even though the implementation of antibiotic stewardship programs (ASP) in pediatrics has been shown to reduce antibiotic use, this implementation has been limited to large university hospitals in Germany. Telemedicine applications might be an effective approach to implement ASP in non-university settings.

**Methods:**

This protocol details the TeleKasper study (Telemedical Competence Network “Antibiotic Stewardship in Pediatrics”). Tele-Kasper is a stepped-wedge cluster-randomized trial that will be conducted across non-university children’s hospitals in Germany. The intervention consists of a telemedical consultation service in the form of a network in different German areas, using an app as a communication tool. The primary outcome will be a 20% reduction in overall antibiotic consumption measured using defined daily doses per 100 patient days.

**Discussion:**

The TeleKasper study aims to implement and evaluate a prototype for a nationwide antibiotic stewardship program by telemedical means in pediatric departments in non-university hospitals in Germany to promote rational antibiotic use and improve medical care for infections.

**Trial registration:**

German Clinical Trials Register (DRKS) DRKS00028534. Registered on 22nd of April 2022.

**Supplementary Information:**

The online version contains supplementary material available at 10.1186/s13063-024-08493-z.

## Background

According to the World Health Organization (WHO), antimicrobial resistance (AMR) is recognized as one of the leading health problems [1]. More than 700,000 people worldwide currently die as a result of antimicrobial resistance and it is estimated that AMR will be associated with the deaths of 10 million people per year by 2050 [2]. Overuse and misuse of antibiotics are some of the driving factors in AMR [1, 3].

This is also the case in pediatric patients, as infections make up a very high proportion of all treatment indications. One of the main causes of this problem is the untargeted, non-restrictive, and non-guideline-based widespread use of antibiotics in inpatient [4] and outpatient [5] pediatric settings.

In 2007, the Infectious Disease Society of America (IDSA) published recommendations for the implementation of antibiotic stewardship programs (ASPs) in pediatrics [6]. This concept has since been realized in some pediatric hospitals [7, 8]. The correct implementation of ASPs in pediatrics has been shown to reduce antibiotic use without compromising treatment safety [9]. However, to date, ASP in the pediatric field have been almost exclusively introduced in large university hospitals. This is mainly because non-university pediatric hospitals are limited in terms of the number of beds and number of staff. Furthermore, ASP for adults cannot be easily adopted to children due to the specific characteristics of pediatric patients. In addition, regional hospitals often lack specifically trained infectious disease personnel to ensure high-quality and efficient care for patients, especially those with complicated infectious diseases [10, 11].

Studies of telemedicine applications of ASP have shown that infectious disease consultations are technically feasible and have good adherence to recommendations when users are actively involved in the development [12]. A recent meta-analysis showed that telemedicine-based ASP increased adherence to guidelines and reduced prescription rates, without affecting mortality rates of patients [13]. Also, in a pediatric setting a telemedicine-based ASP was associated with a reduction of antimicrobial use [14].

The overall goal of this study (Telemedical Competence Network “Antibiotic Stewardship in Pediatrics”—TeleKasper) is to counteract the increasing development of antibiotic resistance and to reduce the risk of possible long-term health consequences of uncritical antibiotic use. This is to be achieved through a comprehensive improvement of infectious patient care and indication-based prescription of antibiotics in the pediatric sector. The primary outcome is the reduction of antibiotic consumption in pediatric inpatient care.

## Methods

This protocol was written based on the Standard Protocol Items: Recommendations for Interventional Trials (SPIRIT) checklist [15]. The completed SPIRIT Checklist is included in the Additional file 1.

### Study design

TeleKasper is a stepped-wedge cluster randomized controlled trial that will implement an antibiotic stewardship program in non-university children’s hospitals in Germany. The overall aim is to provide an antimicrobial stewardship program and consultation service to a selection of non-university pediatric hospitals across Germany, thus establishing the seed for a nationwide ASP network. This aims to improve the infectious diseases care of children across the network and support antibiotic stewardship concepts in smaller, non-university children’s hospitals.

The TeleKasper network will consist of several levels including hospital level, hub level, and network leader level. The hospital level will consist of different non-university hospitals. These individual non-university hospitals will be grouped together into regional hubs. Individual non-university hospitals within each regional hub will be coordinated by a hospital with expertise in pediatric antibiotic stewardship and infectious diseases. All regional hubs are in turn grouped together into a network. The network leader is responsible for the overall coordination of the hubs. In this study, four different demographic regions will be investigated, including areas around Munich, Essen, and structurally less resourceful regions around Homburg/Saar and Halle (Saale). Munich is a prosperous megacity surrounded by an extensive rural area. Essen is a metropolitan area with a concentration of cities with high population density. Homburg is a small University town and Halle (Saale) represents a midsize city both in rather structurally disadvantaged regions.

Non-university hospitals within each hub will be randomized at the beginning of the study for inclusion in the intervention phase. The stepped wedge phase starts with a passive phase of 2 months in which no intervention takes place and the care is as usual. Subsequently, the intervention will start in the first hospital. The plan is to introduce the intervention following a standardized onboarding procedure in the first 2 weeks of the month. However, the entire first month of the intervention will be considered as a transition phase and will not be included in the analysis. Each month, a new hospital will begin the intervention. Every hospital that has undergone the on-boarding process will have a full intervention phase of a minimum of 2 months and will be followed up by an additional follow-up phase of 3 months. During this follow-up phase, the intervention (including recruitment of patients for telemedical consultation via app) will resume and data will be collected, but no new hospitals will be included in the study. The overall intervention phase of the study ends with “the last patient” (June 30th, 2024). Additionally, data will be collected in the pre-implementation phase. This data will be used in the analysis of seasonality effects on antibiotic consumption (Fig. 1).

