### Sample size and power calculation

For the sample size calculation, we assumed a lead-in phase of 2 months, a stepped wedge phase of 24 months, and a follow-up phase of 3 months. If 35 hospitals are included, assuming an intervention effect of a 20% reduction in antibiotic consumption, and assuming that 60% of the variance in the hospitals’ monthly consumption data is explained by hospital effects, this would result in a power of 83%. Due to a lack of information, possible effects of seasonality are not considered in the power calculation. However, the stepped wedge design allows this to be taken into account in the statistical analysis. With an effect of 20%, a study with 36 hospitals has a power of 84%, and with 32 hospitals 78%. With the 33 participating hospitals the power would be almost 80%.

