### Statistical analysis

#### Primary outcome analyses

The primary outcome DDDs per 100 patient days will be measured monthly and analyzed using a Poisson mixed-effects model with an intention-to-treat analysis. The intervention, seasonal effects, and calendar time will be included as fixed effects, and the hospitals will be included as a random effect. Data from the transition phase will be excluded from the analysis. Results will be reported as rates per 100 patient days with 95% confidence intervals.

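### Each hospital's pre-implementation consumption is collected, but the stated primary model has no baseline term for it; adding one as a fixed covariate could improve precision, by an amount the document does not fix

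*Protocol article*

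**What the plan says.** The Study design section of the protocol article describes a two-month passive phase, a staggered start of the intervention and a three-month follow-up. It then adds: "Additionally, data will be collected in the pre-implementation phase". The next sentence gives the purpose: "This data will be used in the analysis of seasonality effects on antibiotic consumption". The text does not state how long this phase lasts; Figure 1, cited at that point, is not available here and may show it.

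Under Primary outcome analyses the model is a Poisson mixed model of monthly consumption: "The intervention, seasonal effects, and calendar time will be included as fixed effects, and the hospitals will be included as a random effect". Transition-month data are the only data that this section excludes.

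For power, the Sample size section says "we assumed a lead-in phase of 2 months, a stepped wedge phase of 24 months, and a follow-up phase of 3 months", which makes 29 months with no pre-implementation data. The target effect is a fall of 20%. The variance input reads: "assuming that 60% of the variance in the hospitals’ monthly consumption data is explained by hospital effects". Stated power is 83% with 35 hospitals, 84% with 36, 78% with 32, and just under 80% with the 33 that take part.

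**The concern.** Under the plan's own 60% assumption, a hospital's earlier consumption is a strong predictor of its later consumption. The trial collects it from before any intervention, yet the only use named is seasonality, and the listed model terms include no hospital baseline. The hospitals that cross over first have just the two passive months as their own usual-care data inside the trial window.

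Power with 33 hospitals has no slack. A baseline adjustment could recover some precision without another hospital or month. The text also leaves the role of these months in the primary model open, and the Blinding section says that the analysts are not blinded. That choice is better fixed in advance than made during analysis.

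**Working it through.** **Inputs from the article.** 33 hospitals; 2 + 24 + 3 = 29 months; transition month dropped; hospital share of variance 0.60; 20% reduction.

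**Assumptions.** Two-sided 5% level; normal approximation to the Poisson model; one fixed effect per calendar month; pre-implementation phase of 12 months unless stated. Three roll-outs: starts spread evenly over months 3-24; evenly over months 3-26; and four per month in months 3-11. The last follows from one hospital per hub per month in four hubs, since 33/4 rounds up to 9 months.

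**1. The plan's power.** No standard deviation is given, so this check depends on one unstated input. The method is the generalised least squares variance of a stepped wedge with a hospital random intercept and month effects.

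| Hospitals | Stated | Total SD = mean, no month dropped | Calibrated to 83% at 35, transition month dropped (total CV 0.94) |
|---|---|---|---|
| 32 | 78% | 78.7% | 79.6% |
| 33 | just under 80% | 80.0% | 80.8% |
| 35 | 83% | 82.2% | 83% (set) |
| 36 | 84% | 83.3% | 84.1% |

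All are within 2 points. The steps below start from 79% for 33 hospitals.

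**2. What a baseline explains.** With total variance 1, the mean of 12 baseline months has variance 0.6 + 0.4/12 = 0.633. If levels are stable, it explains 0.6/0.633 = 0.947 of the hospital variance and leaves 0.6 × (1 − 0.947) = 0.032. The hospital share of the remaining variance is then 0.032/(0.032 + 0.4), about 7%.

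**3. Gain if hospital levels are stable.** R is the variance of the intervention effect with the baseline data divided by the variance without them. Power = Φ((0.806 + 1.960)/√R − 1.960), where 0.806 is the normal quantile of 0.79.

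| Baseline months | R, starts 3-24 | R, starts 3-26 | Power |
|---|---|---|---|
| 3 | 0.946 | 0.937 | about 81% |
| 6 | 0.906 | 0.891 | about 83% |
| 12 | 0.850 | 0.827 | 85-86% |
| 24 | 0.786 | 0.756 | 88-89% |

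For 12 months: 2.766/√0.850 − 1.960 = 1.04, giving 85%; 2.766/√0.827 − 1.960 = 1.08, giving 86%. With four starts per month, 12 months give R of about 0.95 and power of 81%, a gain of about 2 points. With stable levels, the covariate and the extra-rows approach give the same R in this approximation.

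**4. If hospital levels drift.** The hospital effect is given a correlation that decays each month, and 12 baseline months are used. The covariate column covers both evenly spread roll-outs.

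| Monthly decay | Change in variance, baseline mean as covariate | Change in true variance, months added as rows under a random intercept (starts 3-24 / 3-26) |
|---|---|---|
| none | −15 to −17% | −15% / −17% |
| 1% | about −4 to −5% | +6% / +12% |
| 5% | −1% or less | +18% / +24% |

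The covariate's R was at or below 1.00 in every decay and roll-out setting examined. The extra-rows approach loses precision under drift when starts are evenly spread, because a single random intercept gives old months the same weight as recent ones. With four starts per month, 12 added rows still lowered the variance under decay.

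**The case against.** A reader might infer that the plan restricts these data to seasonality and so throws away its baseline. The text does not support that. It does not say that seasonality is the sole use. Season is itself a term in the primary model, and only the transition month is excluded, so the earlier months may be meant to enter that model. If they did, they would inform each hospital's level as well as the seasonal curve. This part of the objection stands: the months' role is undefined, not ruled out.

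A reader might also infer a gain of 6-7 power points from the plan's own inputs. That figure needs an assumed 12-month phase, evenly spread starts and fully stable hospital levels, none of which the text establishes. It is the favourable end for a 12-month phase.

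Stability is open to doubt. The Discussion describes lockdowns, a rebound in infections, a record RSV season and antibiotic shortages. The 2 + 24 months ending in March 2024 (Trial status) count back to February 2022, so the earlier months fall in the pandemic. Month effects remove shifts shared by all hospitals, but not those specific to one. This is a good reason not to pool the months as ordinary rows. It is a weaker one against a covariate, whose coefficient shrinks when the baseline predicts poorly.

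Finally, an article condenses its analysis plan, so silence on dataset details is no fault. The point does not rest on silence alone: the article states a use for the data and lists the model terms, and a hospital baseline is in neither.

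**Conclusion.** The point holds as a modest, low-cost improvement and not as an error that undermines the trial. The named use is seasonality, the listed model has no baseline term, the power figure takes no credit for the data, and their place in the primary model is unstated.

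The size depends on the length of the phase, the roll-out and the stability of hospital levels. For an assumed 12 months it runs from almost nothing (5% monthly decay) through about 2 power points (four starts per month, or 1% decay) to 6-7 points (stable levels, evenly spread starts). It would be wrong to claim that using these months can never cost precision: that held for the covariate in the settings examined, but not for extra rows under a random intercept. All figures are normal approximations with one effect per calendar month.

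**What to change.** In Study design, state the length of the pre-implementation phase. There and under Primary outcome analyses, state that each hospital's log mean consumption rate in that phase (DDD per 100 patient days) is a fixed covariate in the primary model, and that a sensitivity analysis omits it. The seasonality use can stay. Do not make the addition of these months as outcome rows under a simple random intercept the primary approach; it is a different model, not an equivalent one.

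The cost is a sentence or two, a few lines of code and the formal amendment that the Protocol modifications section requires, with no new data. Since recruitment was due to end in June 2024 and the analysts are unblinded, the change should be dated and fixed before the intervention effect is estimated. The downside is that the gain is small if hospital levels changed between the pandemic-era baseline and the trial.

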**Fig. 1 Fig1:**
[figure not shown]
Stepped wedge study design

### Inclusion/exclusion criteria for participating hospitals

All non-university hospitals in the study region (located in the vicinity of one of the four competence hubs including Munich, Essen, Homburg, Halle (Saale)) were eligible. All non-university hospitals eligible for participation had been contacted during the process of TeleKasper grant preparation and provided a letter of intent. In total, 33 non-university hospitals will sequentially be included in the study by their respective competence hubs (10% of all German non-university hospitals). All study sites are listed on the official TeleKasper website [16]. There were no exclusion criteria.

### Intervention

The intervention will consist of a telemedical consultation service within the nationwide network. We will develop a new web-/smartphone-App which will serve as the main tool of this telemedical study. The app will provide a textbook-style reference guide for physicians. This reference guide will include extensive information on infectious diseases and antimicrobial substances including recommended dosages, adverse reactions, and therapeutic drug monitoring (TDM) aspects, among others. In addition, the app includes an innovative communication tool that enables direct interaction between participating hospitals and competence hubs. Via this novel inter-institutional data- and IT-secure network, participating centers are given the ability to make specific inquiries about patients within the network—a telemedical ID consulting service. Depending on the complexity and urgency of these inquiries, app requests can be categorized into the following options: (a) Tele-Info which is a short and general query and is unrelated to any patient directly or indirectly; (b) Tele-Konsil which is a specific patient-related query and is basically a telemedicine ID consultation; (c) a telemedicine case conference in order resolve a complicated query that involves more experts in the discussion; and (d) request for an on-site consultation. Written informed consent from the patient’s parents/legal guardian is required prior to any patient-related query (Tele-Konsil or telemedicine case conference). The informed consent will be obtained from the physicians of the participating non-university hospitals caring for the individual patient. Documents will be placed in a dedicated study folder on-site and stored for a period of 15 years. No patient-identifying information will be stored in the app.

Furthermore, the app serves as an educational tool where presentations on various important antibiotic stewardship topics are presented as live Zoom seminars to all participating centers on a regular basis that can be viewed on demand.

The effect of the intervention will be compared to the present general standard of care and the goal is to demonstrate a superiority compared to the standard of care.

### Randomization

Computer-generated randomization will be used to determine when each hospital will start the intervention. The randomization will be stratified according to the hubs. This has an organizational advantage, as only one hospital per hub is assigned to the intervention group per month. The trial statistician will carry out the randomization after the selection of the study sites. After randomization, the trial statistician will notify the leaders of the respective hubs, who will subsequently inform the hospitals eligible for intervention. If any hospital drops out during the intervention phase, the next hospital will take over.

### Blinding

The hospitals are randomly allocated to pre-determined dates to switch from usual care (control group) to the intervention (intervention group). Due to the open-label design, blinding is not feasible. In this context, data analysts are not blinded either.

### Outcome measures and their assessment

#### Primary outcome

The primary outcome of the study is the antibiotic consumption. This will be measured using defined daily dose (DDD) per 100 patient days. The data will be provided by the hospital pharmacy using anonymized routine electronic health records. In addition, an analysis is also possible for individual departments of the pediatric hospital. All systemic antibiotics will be included according to the second level of the WHO Anatomical Therapeutic Chemical (ATC) classification system for antimicrobials (J01) [17], as well as the substances rifampicin (J04AB02), oral vancomycin (A07AA09), fidaxomicin (A07AA12), and metronidazole (P01AB01). As part of the data management process, an attempt will be made to identify extreme values and, if necessary, corrections will be made in consultation with the corresponding hospital. As the data are part of routine health data, information should not be missing. Nonetheless, missing data will not be imputed or replaced.

#### Secondary outcomes

Secondary outcomes include consumption of specific antibiotic substance groups using DDD per 100 patient days, mean length of stay on pediatric wards, and overall mortality. Furthermore, a secondary objective of the study is also to evaluate the quality of medical care and the accuracy of prescribing. This will be done through 3-monthly point prevalence studies (PPS). All participating hospitals will be eligible to participate in the general pediatric wards PPS. Some centers will also be eligible to take part in a neonatal PPS, which will be conducted every 6 months. Each participating hospital staff must fill in a survey about their current patients, which antibiotics are prescribed, and the (presumed) working diagnosis. No patient-identifying information will be collected by this survey, and the participants will not be allocated an individual trial identification number. The team of the corresponding hub will evaluate this survey based on the following criteria: appropriate use of antibiotic, appropriate duration and dosage of the antibiotic, and if the correct microbiologic diagnosis was performed. Written informed consent for this questionnaire will be obtained from the patient’s parents/legal guardian by the physicians of the participating hospitals. The survey will be distributed via LimeSurvey [18] and the data is stored securely in the network of Martin Luther University Halle-Wittenberg. Finally, the pathogen and resistance data of each hospital will be monitored. This information will be provided by the hospitals or corresponding laboratories.

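### Prescribing appropriateness in the point prevalence surveys is rated by the hub that advises the hospital and knows its start date, so this secondary outcome is open to assessment bias that adjustment cannot remove

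*Protocol article*

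**What the plan says.** The Secondary outcomes section of the protocol article adds a quality objective to the consumption outcomes: "a secondary objective of the study is also to evaluate the quality of medical care and the accuracy of prescribing". It is served by surveys every three months on general pediatric wards and, in some centers, every six months on neonatal wards. On the rater the article is explicit: "The team of the corresponding hub will evaluate this survey based on the following criteria". The criteria are "appropriate use of antibiotic, appropriate duration and dosage of the antibiotic, and if the correct microbiologic diagnosis was performed".

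Three other sections show how the hub stands to the hospitals it rates:

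- **Study design:** "Individual non-university hospitals within each regional hub will be coordinated by a hospital with expertise in pediatric antibiotic stewardship and infectious diseases".
- **Intervention:** the app contains an "innovative communication tool that enables direct interaction between participating hospitals and competence hubs", so hub staff answer the hospital's clinical queries.
- **Randomization:** "the trial statistician will notify the leaders of the respective hubs, who will subsequently inform the hospitals eligible for intervention".

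On masking, the Blinding section says only: "Due to the open-label design, blinding is not feasible. In this context, data analysts are not blinded either". The survey form carries no patient identifiers. Nothing is said about hiding the hospital, the hub or the survey date from the raters.

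**The concern.** Whether a prescription was appropriate is a matter of opinion at the margin. After crossover, some of the prescriptions surveyed may follow advice that the hub itself gave, and the hub then grades them. Before crossover the hub has given no such advice, and it knows that the hospital is still a control. The likely direction of bias favours the intervention.

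Antibiotic consumption measures quantity. Consumption by substance group says something indirect about prescribing patterns. The PPS is the only listed outcome in which individual prescriptions are judged for appropriateness, so a claim that the network made prescribing better, and not merely less, would lean on these ratings.

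**Working it through.** **Step 1: is the rater independent or masked?** Reading the sections together: the hub coordinates and advises the hospital (Study design, Intervention), its leaders receive the allocation (Randomization), and its team rates the surveys (Secondary outcomes). No section describes masked, cross-hub, independent or duplicate rating. That the PPS raters are unmasked is an inference, because the Blinding section names the data analysts and not the raters. It is a firm inference, since a hub knows when it began to advise each of its hospitals.

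**Step 2: does the open-label design force this?** No. It rules out masking the hospitals. The ratings are made later, from electronic survey records without patient identifiers, and there are four hubs. Someone who does not know the hospital or its status can rate those records.

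**Step 3: can the analysis remove the bias?** Write the rated proportion for hospital i in survey j as

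Y_ij = μ + β_j + θ·X_ij + u_i + e_ij,

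with X_ij = 1 after crossover. If knowledge of crossover moves the ratings by δ, the drift enters as δ·X_ij. It has the same regressor as the true effect, so the estimate has expectation θ + δ. The terms for hospital (u_i) and calendar time (β_j) leave δ untouched. Descriptive percentages carry it as well.

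**Step 4: how large could it be?** The article gives no figure for the PPS, so there is nothing to reproduce, and what follows is illustrative.

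- From the article: 33 hospitals, 3-monthly surveys, a study of 2 + 24 + 3 = 29 months, and a transition month left out (the article states this exclusion for the primary analysis; applied here by analogy).
- Assumed: surveys in months 1, 4, ..., 28 (10 surveys), starts spread evenly over months 3 to 24, every hospital taking part each time, m = 10 patients per survey, π = 0.65 appropriate, ICC ρ = 0.05, drift δ = 5 points.

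This gives 149 control and 171 intervention hospital-surveys; the remaining 10 of 330 fall in a transition month.

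The variance components for a hospital-survey mean are:

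- π(1−π) = 0.65 × 0.35 = 0.2275
- between hospitals: ρ·π(1−π) = 0.05 × 0.2275 = 0.0114
- within a survey: (1−ρ)·π(1−π)/m = 0.95 × 0.2275 / 10 = 0.0216

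Generalised least squares on the model in step 3 gives SE(θ̂) of about 2.9 points. Then:

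- δ/SE = 5/2.9 = 1.72
- a shift of exactly this size has two-sided p of about 0.08 to 0.09
- chance of p < 0.05 with no true effect: Φ(1.72 − 1.96) + Φ(−1.72 − 1.96) ≈ 0.41, against a nominal 0.05

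Varying the assumed survey size, with the rest fixed:

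| Patients per survey | Adjusted SE (points) | 5-point drift in SE | Chance of p < 0.05 |
|---|---|---|---|
| 5 | 3.9–4.0 | about 1.3 | about 0.25 |
| 10 | 2.9 | about 1.7 | about 0.41 |
| 20 | 2.1 | about 2.4 | about 0.66 |

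At 10 patients per survey, an ICC anywhere from 0.01 to 0.20 leaves the SE between about 2.5 and 2.9 points, depending on the rollout assumed.

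**The case against.** The case on the other side has four parts.

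- **Weight of the outcome.** It is secondary, and the Secondary outcomes analyses section plans descriptive statistics for it, with regression only where applicable. No confirmatory claim depends on it. This stands and limits the seriousness, although a biased percentage stays biased when it is only described.
- **Size.** Survey size, proportion appropriate, ICC, rollout and drift are all assumed. Hospitals are only eligible to take part, and parental consent is needed, so the surveys may be fewer. This stands: the direction can be argued from the article, the magnitude cannot.
- **The full protocol may say more.** The article cites a protocol version 2.0 that is not shown, which could hold a rating manual or duplicate rating. That is possible, but the article does not leave the rater open. It names the hospital's own hub.
- **Independence of the alternative.** The other hubs deliver the same network intervention, so cross-hub rating does not give full independence. This also stands. It removes self-endorsement and knowledge of crossover, but not a shared view of what good prescribing is.

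A reader might go further and infer that a modest drift would produce a significant result on its own. The figures do not support that. Only the SE that ignores hospitals and calendar time, √[0.02275 × (1/149 + 1/171)] ≈ 1.7 points, puts 5 points near 3 SE, and that is not a valid analysis of a stepped wedge. On the adjusted SE the drift is about 1.7 SE, short of significance by itself.

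**Conclusion.** The concern holds for the PPS appropriateness outcome and for nothing else. The article assigns a judgement rating to the party that delivers the intervention and knows the crossover date, without masking, and modelling cannot recover what is lost. Under the stated assumptions, a 5-point drift would raise the false-positive rate from 5% to roughly 40%, or from about 25% to 66% across 5 to 20 patients per survey. These figures show that a drift of that size would matter; they do not estimate one.

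It would be wrong to infer that the trial's main result is compromised. Antibiotic consumption comes from hospital pharmacy data, and neither it nor length of stay or mortality is rated by the hub. The change should be made, but the validity of the primary analysis does not depend on it.

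**What to change.** Have each PPS record rated by one of the other three hubs, on the same criteria, with hospital, hub, exact survey date and intervention status removed. Attach local resistance information in coded form. Attach also a coded supply-shortage period: the Discussion reports shortages of first-line antibiotics in 2022 and 2023, and a rater without that knowledge could mistake a forced substitution for a poor choice.

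The timing matters. According to Trial status, the intervention phase was due to end in March 2024 and the last patient to be recruited by 30 June 2024; the article appeared on 14 October 2024. Many or all surveys may already have been rated. For those, re-rate the stored records, or a random sample of them, in the same masked cross-hub way, and report agreement between the two ratings separately for control and intervention periods. Agreement that differs between the periods would point to the drift described here.

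For surveys not yet rated, the cost is re-routing records among existing teams. For those already rated, it is additional rater time, which sampling can contain. Raters will have less local context, and the coded shortage period gives away a little about calendar time. They will also still belong to the same network, which should be stated as a remaining limitation wherever PPS results are reported.
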